##### Secondary outcome 3: tolerance

Outcome 3: tDCS tolerance questionnaire scores measured after tDCS will be compared between the active tDCS and sham tDCS groups using mean comparison tests.

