##### Objective 3: tolerance

Objective 3 is to compare the clinical tolerance of active tDCS versus sham measured with adverse effects questionnaires in patients with recent-onset schizophrenia at the end of the tDCS treatment.

We hypothesize that subjects randomly allocated to the active group will demonstrate no significant difference in questionnaire scores than subjects randomly allocated to the sham group.

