##### Secondary outcome 3: tolerance

Outcome 3 is the score after the last tDCS session in the following tolerance measures:tDCS-AEQ (adverse effects questionnaire) [42]VAMS (visual analog mood scale) [43].

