### Sample size {14}

Based on previous tDCS studies in patients with schizophrenia (rev. in [17], we assume that a third (33%) of participants in the active tDCS group and 5% of participants in the sham tDCS group will be responders (improvement greater than or equal to *Z*=0.5 from baseline on the MCCB total score). Based on this estimated difference, we calculated that 60 patients are required to demonstrate a difference between the two groups with a power of 80% (*p* = 0.05).

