#### tDCS adverse effects questionnaire (tDCS-AEQ)

The tDCS-AEQ is the most frequently used questionnaire to measure the most reported side effects of tDCS (headaches, neck pain, mood alterations, and seizures, rated by the participant on a scale of 0 to 5) [42].

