## Statistical methods

### Statistical analysis plan

In general, the normality of the data distributions will be investigated with Shapiro-Wilk tests. Between-group comparisons will be performed with Mann-Whitney *z*-tests and two-sample *t*-tests for non-normal and normal continuous outcomes, respectively. Categorical data will be compared with chi-square tests. Both intention-to-treat and per-protocol analyses will be conducted. In case of significant interactions, post hoc analyses will be conducted using appropriate contrasts. Analyses will be adjusted or stratified by the study site as part of a sensitivity analysis. The significance threshold will be set at *P*-value < 0.05 and appropriate effect sizes of significant results will be calculated.

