### Adverse event reporting and harms {22}

Safety assessment will be conducted according to the requirements of the MDR 2017/745 and MDCG 2020-10/1 statements (European commission) and article of the R1123-46 (French Public Health Code). The investigator will document in the CRF any adverse event observed of reported by the participant. The causal link with the use of the medical device (tDCS) will be assessed. Any adverse event will be monitored until it is completely resolved.

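### Objective 3 is judged by a non-significant mean comparison of questionnaire scores that include a seizure item; seizures should be counted by arm within that conclusion instead

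*Protocol article*

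**What the plan says.** - **Objective.** Objective 3 compares clinical tolerance between arms, measured with adverse effects questionnaires at the end of treatment. The stated expectation is that the active arm "will demonstrate no significant difference in questionnaire scores than subjects randomly allocated to the sham group". No margin is given.
- **Endpoint.** Under Outcomes {12}: "Outcome 3 is the score after the last tDCS session in the following tolerance measures". The measures listed are the tDCS-AEQ and a visual analog mood scale. No total score is named for the tDCS-AEQ.
- **Instrument.** The tDCS-AEQ section lists its content as "headaches, neck pain, mood alterations, and seizures, rated by the participant on a scale of 0 to 5".
- **Analysis.** Under Statistical methods {20a}: "tDCS tolerance questionnaire scores measured after tDCS will be compared between the active tDCS and sham tDCS groups using mean comparison tests". The general rules add: "Between-group comparisons will be performed with Mann-Whitney *z*-tests and two-sample *t*-tests for non-normal and normal continuous outcomes, respectively". They also say: "The significance threshold will be set at *P*-value < 0.05".
- **Adverse events.** Under Adverse event reporting and harms {22}: "The investigator will document in the CRF any adverse event", whether observed or reported, with assessment of the link to the device and follow-up to resolution. The data monitoring committee section {21a} adds an independent review of safety at least once a year.

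**The concern.** The endpoint, the test and the expected result for objective 3 are all fixed in the article, and together they fit one of the instrument's own items poorly. Headache, neck pain and mood change are graded symptoms, for which comparing average ratings is reasonable. A seizure either happened or did not, and if it happened its importance does not depend on the arm's average.

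With 30 participants per arm, a few seizures in one arm and none in the other can leave the comparison non-significant, and non-significance is exactly the result that the hypothesis predicts. Adverse events are recorded separately, but neither the general analysis section nor the sections on outcome 3, additional analyses and missing data say that those records bear on the tolerance conclusion. At stake is whether the published tolerance statement would reflect the most serious item on its own questionnaire.

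**Working it through.** **The plan's own figure.** The article gives no figure for outcome 3; its only sample size figure is for the primary outcome: "we assume that a third (33%) of participants in the active tDCS group and 5% of participants in the sham tDCS group will be responders", with 60 patients and 80% power. For two proportions with pooled variance under the null, two-sided 0.05, no continuity correction:

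n per arm = [1.96 × √(2 × 0.19 × 0.81) + 0.8416 × √(0.33 × 0.67 + 0.05 × 0.95)]² / 0.28² = (1.087 + 0.436)² / 0.0784 ≈ 29.6, so 30 per arm and 60 in total.

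The figure reproduces, which confirms 30 per arm as the size to use below. It was not chosen with tolerance in mind.

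**Seizure item alone.** Assumptions not in the article: all 30 per arm contribute a score, each seizure is rated 5, and everyone else is rated 0. With k seizures in the active arm and none in sham:

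- mean difference = 5k/30
- active-arm variance v = 25 × (k/30) × (1 − k/30) × 30/29; sham variance 0
- standard error = √(v/30), t = difference / standard error, 58 degrees of freedom

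For k = 3: difference 0.50, v = 2.328, standard error 0.279, t = 1.80, P = 0.078.

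| Seizures, active vs sham | t-test P | Mann-Whitney P | Fisher two-sided P |
|---|---|---|---|
| 1 vs 0 | 0.32 | 0.33 | 1.00 |
| 2 vs 0 | 0.16 | 0.16 | 0.49 |
| 3 vs 0 | 0.078 | 0.081 | 0.24 |
| 4 vs 0 | 0.039 | 0.042 | 0.11 |
| 5 vs 0 | 0.019 | 0.021 | 0.052 |
| 6 vs 0 | 0.009 | 0.011 | 0.024 |

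The rating of 5 is not critical here. Any common rating cancels from t, and unequal ratings lower it: ratings of 5, 3 and 1 give t = 1.56 and P = 0.12.

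**If the items were summed.** The article does not say so; this shows only the direction. Let s be the standard deviation of the other items' sum, assumed 1 to 4 points and equal in both arms, with those items balanced. Then t = (5k/30) / √[(s² + v)/30 + s²/30]. For 3 vs 0:

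| s | t | P |
|---|---|---|
| 1 | 1.32 | 0.19 |
| 2 | 0.85 | 0.40 |
| 3 | 0.61 | 0.55 |
| 4 | 0.47 | 0.64 |

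Significance is first reached at 6 vs 0 for s = 1 and 8 vs 0 for s = 2; 8 vs 0 is still non-significant for s = 3 (P = 0.13) and s = 4 (P = 0.24).

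**What a count would show.** Three of 30 is 10%, exact (Clopper-Pearson) 95% interval about 2% to 27%. None of 30 has an upper limit of 1 − 0.025^(1/30) = 11.6%. A reader sees both the events and how little 30 participants can exclude.

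**Who contributes a score.** Outcome 3 is scored after the last session. The section on discontinuing interventions {11b} withdraws participants who stop tDCS, and the section on missing data {20c} requires an assessment after the 10 sessions. A participant who stopped after a seizure might therefore supply no outcome 3 score. The table above is the favourable case in which everyone does.

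**The case against.** Four points can be made on the other side.

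1. **Aggregation.** A reader might infer that a seizure is averaged with headache in a single score. The article does not support that. It names total scores for many symptom scales but none for the tDCS-AEQ, and the analysis sentence speaks of scores in the plural. Item-by-item comparison is equally consistent with the text. This stands, and for that reason the lead figure is for the seizure item alone.

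2. **The test is not the cause.** The low sensitivity comes from 30 per arm and rare events. Fisher's test on counts is non-significant up to 5 vs 0, so on this scoring the mean comparison reaches significance sooner. This also stands. It rules out a different significance test as the remedy, but it does not make non-significance a suitable criterion for such an event.

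3. **Safety is covered elsewhere.** A reader might infer that seizures would be hidden. They would not be: events are documented, assessed for causality and followed; an independent committee reviews safety; serious adverse effects permit unblinding {17b}; adverse reactions are evaluated for 3 months {30}. Objective 3 is also limited to questionnaire-measured tolerance and does not claim to override those records. This removes any charge of concealment. What remains is that the objective 3 conclusion, as framed, does not draw on them.

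4. **Table detail belongs in an analysis plan.** True of layouts, and their absence is no fault in an article. The criticism is of what the article does state: a mean comparison for these scores and an expected result framed as non-significance.

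**Conclusion.** The point holds in a limited form and is minor. Objective 3 is tied to a non-significant mean comparison on an instrument that includes seizures. With 30 per arm, all scores present and each seizure rated 5, up to three seizures against none would be compatible with the tolerance hypothesis as worded (P = 0.078 by t-test, 0.081 by Mann-Whitney). Summing items would raise that number, but this rests on an aggregation and a standard deviation that the article does not give. Separately, with no margin and no interval, a non-significant difference does not show equal tolerance for any item. The documents do not support saying that seizures would go unrecorded, or that the mean test is less sensitive than a test on counts.

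**What to change.** In both sections headed Secondary outcome 3 (Outcomes {12} and Statistical methods {20a}):

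- Do not analyse the seizure item by mean comparison. Report the number of participants with a seizure in each arm, with an exact 95% confidence interval, over all treated participants, using both the questionnaire item and the adverse event records kept under {22}. State that this is part of the objective 3 conclusion.
- Keep mean comparisons for the graded symptoms, and give the between-arm difference with a confidence interval.
- State, and reflect in the hypothesis under Objective 3, that a non-significant difference will not be read as showing equal tolerance.

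The data are already collected. The cost is a few sentences and one extra descriptive table. No significance test on seizure counts is proposed, since it would be uninformative at this size.

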**Method:**

The study is designed as a randomized, double-blind, 2-arm parallel-group, sham-controlled, multicenter trial. Sixty participants with recent-onset schizophrenia and cognitive impairment will be randomly allocated to receive either active (*n*=30) or sham (*n*=30) tDCS (20-min, 2-mA, 10 sessions during 5 consecutive weekdays). The anode will be placed over the left dorsolateral prefrontal cortex and the cathode over the left auditory cortex. Cognition, tolerance, symptoms, general outcome and EAP (measured with EEG and multimodal MRI) will be assessed prior to tDCS (baseline), after the 10 sessions, and at 1- and 3-month follow-up. The primary outcome will be the number of responders, defined as participants demonstrating a cognitive improvement ≥*Z*=0.5 from baseline on the MATRICS Consensus Cognitive Battery total score at 1-month follow-up. Additionally, we will measure how differences in EAP modulate individual cognitive benefits from active tDCS and whether there are changes in EAP measures in responders after active tDCS.

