### Trial design {8}

The present study is designed as a superiority, double-blind, parallel-group, sham-controlled randomized clinical trial with an allocation ratio of 1:1. Study sites will include 4 University Hospital centers in France. In a 1 × 2 factorial design with sham, patients are randomized into two groups: active tDCS and sham tDCS. A total of 60 patients with schizophrenia will be randomly assigned to receive either active tDCS (*N*=30) or sham tDCS (*N*=30). Psychiatric and neuropsychological assessments will be performed at baseline (time of consent), at the end of the tDCS procedure, and at 1 and 3 months following the end of the tDCS procedure (maintenance effect). Auditory biomarker analyses will involve neurobiological measures (multimodal magnetic resonance imaging and neurophysiology) recorded at baseline and at 1 month after tDCS. Study schedule and study flowchart are presented in Figs. 1 and 2.

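### The tolerance comparison (outcome 3) uses post-treatment scores with no baseline term, and the abstract and body disagree on when tolerance is measured; the cost is precision, not validity

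*Protocol article*

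**What the plan says.** The body of the protocol article is consistent about outcome 3. Objective 3 places the tolerance comparison at one time point: "measured with adverse effects questionnaires in patients with recent-onset schizophrenia at the end of the tDCS treatment". The Outcomes section defines the variable the same way: "Outcome 3 is the score after the last tDCS session in the following tolerance measures". It names two instruments, the tDCS-AEQ and the VAMS. The statistical section then specifies the analysis: "tDCS tolerance questionnaire scores measured after tDCS will be compared between the active tDCS and sham tDCS groups using mean comparison tests".

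The abstract's Method paragraph reads differently: "Cognition, tolerance, symptoms, general outcome and EAP (measured with EEG and multimodal MRI) will be assessed prior to tDCS (baseline), after the 10 sessions", followed by the 1- and 3-month visits. Taken literally, this gives tolerance a baseline assessment and two follow-up assessments that the body does not describe.

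Three other statements bear on the point:

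- The tDCS-AEQ is described as covering "headaches, neck pain, mood alterations, and seizures, rated by the participant on a scale of 0 to 5", and these are presented as side effects of stimulation.
- The hypothesis for Objective 3 is that the active group "will demonstrate no significant difference in questionnaire scores than subjects randomly allocated to the sham group".
- The section on additional analyses {20b} allows covariate adjustment only when the arms turn out to differ at baseline. Its examples are antipsychotic dosage, illness duration and age.

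**The concern.** Headache, neck pain and mood can differ between patients before any current is applied. The VAMS is a mood scale and the tDCS-AEQ includes mood alteration, so part of the spread in post-treatment scores may have been there at the start. A comparison of raw post-treatment means leaves that spread in the error term. The mixed models for outcomes 2b to 2d at least include the pre-treatment visit; the analysis of outcome 3 does not.

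Precision matters here because the hypothesis is one of no significant difference. The less precise the comparison, the more easily a non-significant result arises, whatever the true difference in tolerance. A tighter interval would show more clearly which differences the data still allow.

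There is also a plain inconsistency. If the abstract is right, a natural covariate is collected and not used. If the body is right, the abstract describes assessments that do not take place.

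**Working it through.** **Inputs.** Arm size is 30 and 30, allocation 1:1 (Trial design {8}). The significance threshold is 0.05 (Statistical analysis plan section), taken here as two-sided. The documents give no figure for the tolerance comparison, so there is none to reproduce; the stated sample size of 60 concerns the responder outcome. The correlation r between baseline and post-treatment score is not given either. It is assumed, over the range 0.2 to 0.7. Complete data are assumed, and differences are in units of the between-patient SD of the post-treatment score.

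**Half-width as planned.** t(0.975, 58 df) × √(2/30) = 2.0017 × 0.2582 = 0.517 SD.

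**Half-width with baseline adjustment.** ANCOVA multiplies the residual variance by (1 − r²) and uses one more degree of freedom: t(0.975, 57 df) × √(2/30) × √(1 − r²), with t = 2.0025. Power is for a true difference of 0.5 SD, from the noncentral t distribution.

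| r (assumed) | 1 − r² | 95% CI half-width (SD) | Power for 0.5 SD |
|---|---|---|---|
| post-only, as planned | 1 | 0.517 | 48% |
| 0.2 | 0.96 | 0.507 | 49% |
| 0.3 | 0.91 | 0.493 | 51% |
| 0.5 | 0.75 | 0.448 | 59% |
| 0.7 | 0.51 | 0.369 | 76% |

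The interval therefore shrinks by about 2% at r = 0.2 (1 − 0.507/0.517) and by about 29% at r = 0.7 (1 − 0.369/0.517).

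**Why ANCOVA and not a change score.** The variance of a simple change from baseline is 2(1 − r) times that of the post-treatment score. This is 1.4 at r = 0.3, 1.0 at r = 0.5 and 0.6 at r = 0.7. An unadjusted change score would thus be worse than the current plan below r = 0.5. ANCOVA loses nothing at any r beyond one degree of freedom.

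**How far the abstract can be trusted on timing.** Its sentence attaches one list of visits to all domains. For the auditory-processing measures, that list conflicts with Trial design {8}, which has them "recorded at baseline and at 1 month after tDCS" and at no other visit. The sentence is therefore already inexact for one domain. No part of the body describes a baseline tDCS-AEQ or VAMS, and the participant timeline figure that might settle the matter is not shown in the text reviewed.

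**A covariate that does not depend on the abstract.** The CDSS is an outcome 2c measure analysed as change from baseline, and the outcome 2c model includes the pre-treatment visit. A baseline depression score will therefore be available for every patient assessed at baseline.

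**The case against.** The strongest reply is that nothing here is an error. The arms are randomised, so a comparison of post-treatment means is unbiased with correct error rates, and adding a covariate to a secondary outcome is an efficiency choice. The first part stands in full; the loss is precision only. The second part is weaker, because the article fixes the test explicitly, and the change is nearly free.

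A reader might infer three stronger things that the documents do not support:

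- *That the trial collects baseline tolerance scores and discards them.* This rests on the one abstract sentence shown above to be loose. The supportable statement is that the abstract and the body must be reconciled.
- *That a chance baseline imbalance is a separate harm that biases the result.* The unadjusted interval already allows for such imbalance, so counting it again would count one efficiency loss twice.
- *That the gain is large for both instruments.* The tDCS-AEQ asks about side effects of stimulation. A score taken before stimulation may not exist, or may predict the later score poorly. At r = 0.2 to 0.3 the gain is small. The argument is better suited to the VAMS.

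It may also be said that {20b} already provides for adjustment. It does so only when an imbalance is observed, so it does not recover precision in general, and its examples do not include baseline mood or tolerance.

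The CDSS is an imperfect substitute: it is clinician-rated and covers two weeks, and the documents give no correlation between it and the VAMS. It has no evident link to the pain items. The gains in the table cannot be carried over to it.

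**Conclusion.** The point holds as a modest loss of precision together with an inconsistency about timing. The planned test is valid. With 30 per arm, baseline adjustment would shorten the 95% interval half-width from 0.517 SD to between 0.507 and 0.369 SD over assumed correlations of 0.2 to 0.7. The true correlation is unknown, is likely higher for the VAMS than for the tDCS-AEQ, and decides whether the gain is trivial or useful. These figures assume complete data and a baseline measurement of the same scale. Severity is low because tolerance is a secondary outcome. The change is still worthwhile because the hypothesis is one of no significant difference, which makes the width of the interval the informative part of the result.

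**What to change.** 1. Reconcile the abstract with Objective 3, the definition of outcome 3 and its analysis section: state whether the VAMS and the tDCS-AEQ are each completed before the first session, and whether tolerance is rated at 1 and 3 months.
2. If a baseline VAMS is taken, replace the mean comparison with ANCOVA of the post-treatment VAMS on arm and baseline VAMS. Do the same for the tDCS-AEQ if a pre-session score is taken. Report each adjusted mean difference with its 95% confidence interval.
3. If no baseline VAMS is taken, adjust the post-treatment VAMS for baseline CDSS and expect a smaller gain. Leave the tDCS-AEQ as a post-only comparison if it has no pre-session score, and report its difference with a 95% confidence interval.

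The cost is a change of wording, one degree of freedom per model and slightly more analysis work. No new data are needed if the abstract is right or if the CDSS is used. Choosing to add pre-session ratings would mean two short self-ratings per patient.

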##### Secondary outcome 4: response markers and predictors

Outcome 4a: the difference at baseline between responders and non-responders in EAP measures will be analyzed using mixed effects regression models with cognitive improvement status (responder or non-responder) and group (active or sham) as independent variables.Outcome 4b: the changes from baseline to 1-month follow-up in EAP measures will be analyzed using mixed effects regression models with cognitive improvement status (responder or non-responder), group (active or sham), and time (before tDCS and 1-month follow-up) as independent variables.

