##### Objective 4: response markers and predictors

Objective 4a is to assess how differences in EAP mechanisms modulate individual cognitive benefits from active tDCS measured with a range of EAP measures in patients with recent-onset schizophrenia at 1-month follow-up.Objective 4b is to evaluate whether there are changes in EAP measures in patients associated with cognitive improvement after active tDCS at 1-month follow-up.

We hypothesize that baseline EAP measures will distinguish between participants who have improved cognitive deficits after active tDCS and those who do not, and that changes in EAP measures after tDCS will be only observed in participants with improved cognitive deficits after active tDCS.

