##### Secondary outcome 4: response markers and predictors

Outcome 4a is the differences at baseline in the following EAP measures between patients with cognitive improvement and patients without cognitive improvement after active tDCS:Correlations (*z*-scores) between left prefrontal and temporal cortical areas (i.e., areas stimulated with tDCS) measured with resting-state functional magnetic resonance imaging (MRI).Spectral power (dB) and inter-assay coherence (%) in gamma frequency (40-Hz) during specific auditory paradigms (auditory steady-state, oddball, tone-matching) measured with electroencephalography (EEG).GABA and glutamate levels (mM) within left prefrontal and temporal cortical areas measured with resting-state Magnetic Resonance Spectroscopy (MRS)radiotracer binding potential on GABA-A receptors (Binding Potential) within left prefrontal and temporal cortical areas measured with resting-state [^11^C]flumazenil positron emission tomography MRI (PET-MRI).

Outcome 4b is the changes between baseline and 1-month follow-up in the same EAP measures in patients with cognitive improvement compared to patients without cognitive improvement after active tDCS.

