## Discussion

The present study is a double-blind, sham-controlled, parallel-group trial designed to investigate the efficacy and tolerance of left fronto-temporal transcranial direct current stimulation (tDCS) as a treatment of cognitive impairment in a multicenter sample of patients with recent-onset schizophrenia. Given the causal role of cognitive defect in daily functioning [57, 58], the utilization of safe and potentially effective neuroenhancement tools such as tDCS for the rehabilitation of cognitive impairment in the early stages of schizophrenia may help to improve the outcomes of the disorder. As the contribution of EAP deficits to cognitive and functional outcomes is increasingly demonstrated [10–12], we will evaluate for the first time the impact of targeting the auditory cortical areas (instead of the temporo-parietal junction) on cognitive response. While several RCTs have already been conducted to test the efficacy of tDCS on cognitive impairment in schizophrenia, most of them were limited by the lack of maintenance effects assessment and small sample size [17]. Here, besides proposing a new fronto-temporal tDCS protocol by targeting the auditory cortical areas, we aim to conduct an RCT with follow-up assessments up to 3 months.

In addition, this study will allow identifying and assessing the value of a wide range of neurobiological EAP measures for predicting and explaining cognitive deficits improvement after tDCS. Alterations in EAP have been demonstrated to lead to poor functional outcomes associated with impaired cognition in patients [10–12], which makes EAP a relevant biomarker for cognitive response. The search of predictive and explanatory biomarkers of clinical response to tDCS is an expanding domain with the potential to improve therapeutic plans offered to patients with schizophrenia, while improving our understanding of underlying tDCS mechanisms of effect on cognitive deficits. The results of this study will streamline participant selection in subsequent tDCS trials, thereby enhancing treatment outcomes and reducing costs through a precision medicine approach. Limitations of this trial include the time commitment needed from participants and investigators, stringent exclusion criteria, risk of dropout during the study, and the possibility that the entire sample will not meet the cut-off for cognitive response.

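### Outcome 4a can report a marker that is merely associated with cognitive gain as a predictor of tDCS benefit, because no marker-by-group test is named

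*Protocol article*

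**What the plan says.** All references are to the protocol article.

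- **Objective 4** sets out to "assess how differences in EAP mechanisms modulate individual cognitive benefits from active tDCS". Its hypothesis is narrower: "baseline EAP measures will distinguish between participants who have improved cognitive deficits after active tDCS and those who do not".
- **Outcomes {12}, Secondary outcome 4**, defines 4a as a baseline difference "between patients with cognitive improvement and patients without cognitive improvement after active tDCS". Sham participants are not part of that definition.
- **Statistical methods {20a}, Secondary outcome 4**, states that "the difference at baseline between responders and non-responders in EAP measures will be analyzed using mixed effects regression models with cognitive improvement status" as one independent variable and group (active or sham) as the other. The EAP measure is the response variable. No status-by-group term is named.
- **Statistical methods, Statistical analysis plan**, adds a general rule: "In case of significant interactions, post hoc analyses will be conducted using appropriate contrasts".
- **Discussion** gives the intended use: "The results of this study will streamline participant selection in subsequent tDCS trials".

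**The concern.** In a sham-controlled trial, benefit from tDCS is the active-minus-sham difference. A marker modulates that benefit if the difference varies with the marker. The 4a outcome asks something else: whether the marker differs between people whose MCCB score rose by at least 0.5 Z and people whose score did not.

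A gain of that size need not come from tDCS. The sample size section itself expects 5% responders under sham, and no concomitant care is prohibited. The Introduction describes cognition and EAP as closely linked, so a marker that is related to gain regardless of treatment is plausible. Such a marker would show a responder difference in the active arm with no modulation on the MCCB scale, and the report could present it as a predictor of tDCS response.

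The outcome definition and the model also disagree on whether sham data are used. The sham arm is the only part of the design that can separate the two explanations.

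**Working it through.** **The plan's own figure.** The document gives no power figure for 4a. Its total of 60 for the primary comparison reproduces. Inputs are 33% and 5% responders, two-sided 0.05, power 80%, pooled variance and no continuity correction. The mean proportion is 0.19.

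n per arm = [1.96·√(2·0.19·0.81) + 0.8416·√(0.33·0.67 + 0.05·0.95)]² / 0.28² = (1.087 + 0.436)² / 0.0784 ≈ 29.6, so 30 per arm and 60 in total. Power at 30 per arm is 80.5%. This figure is not in dispute. The same rates are used below.

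**Sham responders.** The expected number is 30 × 0.05 = 1.5. The chance of none is 0.95³⁰ = 21.5%, and a status-by-group term then cannot be estimated. The chance of none or one is 55%. PET is acquired at one centre with 20 planned participants. Assuming about 10 of them are on sham, the chance of no sham responder is 0.95¹⁰ = 60%.

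**Simulation set-up.** There are 30 participants per arm and one standard-normal marker. Gain = r·marker + √(1 − r²)·noise. The active mean is shifted so that one cut-off gives 33% and 5% responders. Tests are two-sided at 0.05. The correlation r is an assumption, because the document gives none, so a range is shown. Trials in which status-by-group cannot be estimated count as non-rejections. Marker-by-group was run on MCCB gain without a baseline MCCB term.

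**Same r in both arms (no modulation on the continuous scale): chance of p < 0.05**

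| Test | r = 0.2 | 0.3 | 0.4 | 0.5 |
|---|---|---|---|---|
| Responder contrast within active | 13% | 24% | 39% | 58% |
| Status effect, additive status + group | 16% | 30% | 49% | 71% |
| Status × group | about 4% | about 4% | about 4% | about 4% |
| Marker × group on continuous MCCB | 4–5% | 4–5% | 4–5% | 4–5% |

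At r = 0 the first two tests reject in about 5%, as they should.

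**Real modulation (r in active as shown, 0 in sham): power**

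| Test | r = 0.4 | 0.5 | 0.6 |
|---|---|---|---|
| Responder contrast within active | 39% | 57% | 77% |
| Status × group | 10% | 13% | 18% |
| Marker × group on continuous MCCB | 34% | 50% | 67% |

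Repeat runs put status-by-group at 10–19% over this range.

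**Marker partly prognostic as well.** With r = 0.5 in active and 0.2 in sham, marker-by-group has about 22% power, against 58% for the within-active contrast. With 0.6 and 0.3 the figures are about 23% and 78%.

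**The case against.** **The model does include sham, and an interaction may be intended.** The models for outcomes 2b to 2d also list only factors, although the effect of interest there is plainly group by time. Read the same way, with the general rule on interactions, 4a would contain status by group. This objection stands in part: it would be wrong to infer that the planned analysis ignores sham. The implied term does hold its error rate, but the second table shows how little it could detect.

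**No modulation is a matter of scale.** This stands. The primary endpoint is a responder proportion. In the scenario of equal r and a common cut-off, the active-minus-sham responder difference is 28 points overall. Above versus below the marker median it is 32 versus 24 points at r = 0.2, and 39 versus 17 at r = 0.5. A reader might infer that selecting on a prognostic marker cannot enlarge the treatment difference. That holds for mean MCCB change, not for the responder difference. Objective 4a does not state a scale.

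**The document makes no false declaration.** This also stands. A reader might infer that prognostic markers are declared tDCS predictors. The text does not say so, and the hypothesis describes the within-active contrast accurately. The aim is secondary. Parallel test forms and a low expected sham response limit non-tDCS gain. The remaining problem is that the modulation objective and the selection claim go further than that contrast supports.

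**Conclusion.** The point holds as a mismatch between question and analysis. Objective 4a and the Discussion need effect modification. The outcome definition gives a one-arm association, and the model names no term that tests modification. The two passages also differ on whether sham is used.

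Under the within-active contrast or the additive model, a marker with no modulation on the continuous MCCB scale is flagged in about 13–58% or 16–71% of trials for r from 0.2 to 0.5, so it can be reported as a tDCS predictor. The charitable interaction reading avoids this but is nearly uninformative.

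These sizes rest on assumed correlations, a normal model for gain, the protocol's 33% and 5% responder rates, and the continuous MCCB scale as the one on which modulation is judged. The primary analysis is not affected. The change is worth making before analysis.

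**What to change.** - In Outcomes {12} and Statistical methods {20a}, name as the 4a test the EAP-by-group coefficient, with its confidence interval. It comes from a regression of continuous 1-month MCCB total score on baseline MCCB, group, the baseline EAP measure and their product.
- Use all randomised participants who have that EAP measure. PET comes from a single centre with about 20 participants, so report it descriptively.
- State that modulation is assessed on the continuous MCCB scale.
- Keep the responder versus non-responder comparison as descriptive, labelled as associated with cognitive gain, and align the two sections on the use of sham.
- If the within-active contrast is kept as the main 4a result, drop the modulation and selection claims.

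The change is to wording and analysis only, with no new patients or measurements. The price is power. If the marker is unrelated to gain under sham, the loss against the within-active contrast is about 5 to 10 points (39 − 34, 57 − 50, 77 − 67). If the marker is also partly prognostic, the loss is much larger (22–23% against 58–78%), although the within-active figure then includes detection of the prognostic part. A non-significant interaction should therefore be reported as inconclusive, not as absence of modulation.
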